#### Selection criteria and recruitment approach

A standard process of selection and consent-taking will be undertaken at each study site comprising potential study participants for each of the above categories of individuals (including vulnerable populations). A recruitment approach will follow, and the main actors who will facilitate the recruitment process of the potential target respondents for this research are (a) selected service providers, (b) CHWs—working in the catchment area of the selected service providers, (c) community-based opinion leaders, that is, male, and female schoolteachers, social activist/non-governmental organization (NGO) workers. The country Principal Investigator (PI)/Co-PI will train all of them on the study’s main objectives, purpose, issues in ethics and the importance of consent.

### Qualitative data management and analysis

At the country level, the study will engage a team of reseachers with expertise in qualitative methods and local dialects.

The interviews will occur in a private location guaranteeing confidentiality. We anticipate that interviews will last between 45 and 60 mins and will take place in a safe, neutral space of the participant’s choosing (eg, town hall, office space, on porch outside participant’s home, etc). The interviews will be recorded with the participants’ informed consent. Research assistants proficient in transcription will transcribe and translate the audio recordings into English. Accuracy checks will be conducted by comparing the transcripts with the original audio files.

To conduct thematic analysis, qualitative research management software like QSR NVivo V.12 or Atlas.ti will be used. This involves creating a primary codebook to outline all nodes and using it to code the collected data. As analysis progresses, new nodes will be incorporated into the codebook to capture emerging themes and concepts identified during coding. The data will be coded by research assistants skilled in using Nvivo. To ensure coding quality, inter-rater reliability will be assessed by calculating the Cohen’s Kappa coefficient, with a threshold of 0.8 or higher considered acceptable for concordance.

During the intervention design workshop, the findings from the formative phase will be shared and discussed with key research team members, clinicans and clients. The aim is to inform the development of a contextually sensitive package of contraceptive counselling interventions from a bottom-up approach. Each workshop participant’s perspectives will be taken into account when assessing the potential effectiveness, feasibility, acceptability to women and providers, integration into family planning programmes, sustainability and scalability of potential interventions.

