### Qualitative research

#### General design

For the qualitative research components of the study during the formative and reflective phases, we will conduct in-depth interviews (IDIs) in Pakistan and Nigeria with various community members (including women, adolescent males and females, partners and influential individuals), health personnel (such as clinicians, managers and community health workers—CHWs), development partners, donor agencies and national policymakers. The formative phase will involve selecting four health centres (both public and private) and their respective coverage areas in each country using a convenient sampling approach. These sites will be chosen from the sampling frame established during the pre-formative phase.

To identify barriers and facilitators related to contraceptive counselling, separate IDIs will be conducted with groups of 6–10 participants from the following categories: (1) women who have used family planning services at the health centre within the past 12 months: married and unmarried adolescent females (≤19 years), married and unmarried women 19–39 years, married and unmarried women ≥40 years (The study will include Women of Reproductive Age (WRA)—irrespective of their marital status and age group (including migrants refugee people, ethnic and religious minorities, women or men with disabilities, women or men with HIV, etc are inclusive)); (2) married and unmarried men who are husbands or partners of clients who have used family planning services at the clinic within the past 12 months, and married and unmarried adolescent males (<19 years) and (3) family planning service providers.

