About the recruitment of men/male participants, the women participants will be first recruited based on their eligibility and recruitment criteria. If the female participant is selected, she will be asked whether she is using the FP method in consensus with her male partner/spouse or using it covertly. If she uses the FP method with the consensus of her male partner/spouse, we will recruit the accompanying male partners/spouses in the study. If the women participant is using the FP method covertly, then the women will be first asked to provide consent to be invited to study participation. If she does not consent, then men/male participants will be identified by the CHWs at the community level. In both cases, formal consent will be taken from the woman whether she is using the FP method covertly or in consensus with her male partner/spouse.

IDIs will also take place with clinic managers, supervisors, CHWs, policymakers and other influential individuals/opinion leaders (selected purposively) who have observed, supervised or monitored family planning services at/or the catchment of the selected public/private health facility. We anticipate that interviews will last between 45 and 60 mins and will take place in a safe, neutral space of the participant’s choosing (eg, town hall, office space, on porch outside participant’s home, etc). Both the recruiter and the participant will decide and agree on the location of the interview and this will be conveyed to the research team. Alternatively, the team will also identify pay-per-hour spaces as an option to present to the participant. The interview guides will address several key themes pertinent to contraceptive counselling, including: practices, attitudes and knowledge regarding contraception; health systems and sociocultural challenges and enablers affecting contraceptive use; and quality of care, encompassing autonomy, informed decision-making and other human rights considerations in contraceptive services.

These themes will guide the exploration of participants’ perspectives and experiences related to contraceptive counselling within the broader context of reproductive health services.

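### Client interviews are promised a private, confidential location, yet the porch outside the woman's home is given as a suitable place, and opinion leaders are not kept out of client recruitment

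*Protocol article*

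**What the plan says.** Four statements in the protocol article bear on this point.

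- **Setting.** Qualitative data management and analysis states: "The interviews will occur in a private location guaranteeing confidentiality". The sentence after it allows a safe and neutral place that the participant chooses, with these examples: "eg, town hall, office space, on porch outside participant’s home, etc". General design, under Qualitative research, gives the same list. It adds that "Both the recruiter and the participant will decide and agree on the location of the interview", that the agreed place is then passed on to the research team, and that "the team will also identify pay-per-hour spaces as an option to present to the participant".
- **Who is interviewed.** The first category in General design is "women who have used family planning services at the health centre within the past 12 months". It covers married and unmarried women, with an age band for adolescents.
- **Covert use.** Once a woman has been selected, "she will be asked whether she is using the FP method in consensus with her male partner/spouse or using it covertly". Her answer determines how male participants are found.
- **Who recruits.** Selection criteria and recruitment approach names three kinds of actor who help with recruitment: service providers, community health workers (CHWs), and "community-based opinion leaders, that is, male, and female schoolteachers, social activist/non-governmental organization (NGO) workers". All are to be trained on the study's purpose, ethics and consent.

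**The concern.** For a woman in the client category, membership is itself the sensitive fact: she is there because she used family planning services within the past 12 months. Anyone who sees or overhears a recorded interview of 45 to 60 minutes about contraception may infer her use. The document treats this risk as real. It asks about covert use, adopts privacy and confidentiality as one of its human rights standards, and reports in the Pakistan section that 16% of men thought family planning might encourage promiscuity.

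The protection of these women is the main thing at stake. A secondary stake is the quality of the formative material. If women who fear exposure decline or speak guardedly, the package co-designed from these interviews would have less input from those whose autonomy the study aims to improve. That second effect is plausible, but the documents do not demonstrate it.

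**Working it through.** No arithmetic applies and the plan gives no figure to reproduce. The check sets the statements side by side.

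1. **Each named place against the promise of a private, confidential location.**

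| Place named | Meets the promise? |
|---|---|
| Porch outside the home | No. It is outdoors and next to the household from which a covert user is hiding her use. |
| Town hall | Only if a closed room is used, which the text does not require. |
| Office space | Yes, if closed. |
| Pay-per-hour space | Yes, if closed, but it is offered only as an option. |

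   The porch is the clear conflict. The town hall is the weaker one.

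2. **Do the two location sentences apply to women clients?** Those in Qualitative data management and analysis cover the interviews generally, with no exception for clients. Client interviews occur in both the formative and the reflective phases, so both are affected.

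3. **Are covert users among the women interviewed?** Yes. General design asks selected women about covert use and does not exclude those who report it.

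4. **Does the covert-use question change the setting or the approach?** No. It comes after selection, and its stated consequences concern only the recruitment of men. Nothing links the answer to the place of interview or to the person who contacts her.

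5. **Could a community third party learn of her client status?** The recruitment section does not assign its three channels to particular respondent groups. A service provider may already know who is a client; a schoolteacher or activist would not ordinarily know. If such a person helped to recruit for a client category, that person would have to learn or infer client status. Because General design has the recruiter agree the place and then pass it to the research team, that person could also know where the interview will be held. The text permits this sequence but does not prescribe it.

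**The case against.** The strongest reply on location is that the list is illustrative and the operative rule is a safe, neutral place that the participant chooses. She can refuse the porch, an office or a hired room is available, and a site must satisfy the privacy sentence as well as the list. In General design the location text also sits in the paragraph that opens with managers and policymakers. This softens the point without removing it. The data management section repeats the list for the interviews generally, and a woman's choice does not make a porch confidential. Naming the porch as an example tells sites that it is acceptable.

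On recruitment, the reply largely succeeds. A reader might infer that covert users are to be recruited through schoolteachers. The documents do not say so. The phrase covering every category belongs to the preceding sentence, on selection and consent. The next sentence lists three facilitators without saying who approaches whom, and the respondents also include men, policymakers and influential persons. Opinion leaders may be meant only for such groups. What stands is that client women are not excluded from this channel.

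A condensed article may leave approach procedures to the full protocol or a manual, so the absence of a client-specific procedure is not itself the finding. The finding is the conflict between stated sentences, together with a recruitment list that is worded too openly. Ethics training and committee approval are partial safeguards, but they do not reconcile the text.

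**Conclusion.** The point holds in limited form. The promise of a private, confidential location conflicts with the porch example, and conditionally with the town hall. The open recruitment list adds a possible, not a stated, route of disclosure. The conclusion assumes only that a porch may be seen or overheard by household or neighbours, and that recent use of family planning services is sensitive for some clients, as the covert-use question implies.

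Two stronger readings should not be drawn. First, a reader might try to count the women exposed. The documents give no covert-use share, do not say how many women would choose an unsafe place, and do not say how many would be approached by an opinion leader, so no number is supported. Second, a reader might extend the point to the trial itself. It concerns only the formative and reflective interviews; the cluster trial's sample size, randomisation and analysis are untouched.

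**What to change.** - **General design, and Qualitative data management and analysis:** delete the porch example. State that client interviews take place in a closed private space of the participant's choosing, for instance an office or the hired room already offered. Keep a town hall only where a closed room is used.
- **Selection criteria and recruitment approach:** state that women in the client categories are approached through the service provider or research staff. Opinion leaders would help recruit community and influential respondents only.
- **Order of steps:** agree the place after the covert-use question, and do not share it with community recruiters.

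The cost is a few sentences, some travel for participants and slightly slower recruitment. A stricter rule, with invitations made only by research staff at the health centre, is not recommended. It could miss women who used services within the past 12 months but have not returned. Moving the interviews themselves into the centre could also make clients guarded about the service they are judging.

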### Cluster RCT

The research will be a multi-intervention, three-arm, single-blinded, parallel, cluster RCT done in selected primary health centres (clusters) in Pakistan and in Nigeria (see figure 2 for the cluster RCT flow diagram, and figure 3 for the schedule of enrolment, interventions and assessments (Standard Protocol Items: Recommendations for Interventional Trials template). Centres will be randomly allocated to the three study arms in matched ratios (1:1:1) on the basis of the number of monthly family planning encounters, the number of available contraceptive types, the ratio of health workers per population in the clinic coverage zone, the location in urban or rural settings and selected district-level variables that may have an influence on the study outcomes, including the unmet need for family planning, the level of literacy among women and household income terciles. Only data analysts will be masked/blinded to trial-arm allocation. Service providers skilled in family planning services will implement the clinical components of the contraceptive counselling package.

**Figure 2 F2:**
[figure not shown]
Flow diagram of the cluster randomised controlled trial in each study country.

**Figure 3 F3:**
[figure not shown]
Schedule of enrolment, interventions and assessments for the cluster randomised controlled trial phase in each study country (SPIRIT template). SPIRIT, Standard Protocol Items: Recommendations for Interventional Trials.

#### Outcome measures

Quantitative indicators will be captured in case-report forms (CRFs) developed and piloted at the country level before finalisation. The proposed outcomes to be assessed after each visit, at mid-point (6 months after enrollment) and at the study end (12 months after enrollment) are oriented toward clients and consist of levels of clients’ decision-making autonomy and demand satisfied for family planning.

To determine their level of decision-making autonomy, clients will be asked to answer questions about the different domains contained in the counselling definition (see the Background section). These domains comprise client–provider collaboration, client’s needs and preferences, the quality of information, freedom from coercion, confidentiality and dignity. The PCCC, developed and tested in publicly funded clinics in California, will also be used.^43^ The four PCCC questions fall under the domains of respect, eliciting—and giving serious consideration to—client’s preferences, and information quality and it will be assessed during the intervention phase as per described by UNFPA to measure decision-making autonomy SDG 5.6.1.^44^

The study proposes nonetheless the another outcome, while acknowledging its limitations: modern contraceptive prevalence after the first visit and at 6 and 12 months after enrollment.

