Building on this systematic review, the WHO organised a geographically diverse think tank in May 2019 in Geneva, Switzerland, to identify research and guidance gaps and other opportunities to improve the quality of contraceptive counselling.^32^ Equally important was the crafting of a definition on contraceptive counselling, which was adopted by think tank members^33^ : *Contraceptive counselling is defined as the exchange of information on contraceptive methods based on an assessment of the client’s needs, preferences and lifestyle to support decision-making as per the client’s intentions. This includes the selection, discontinuation or switching of a contraceptive method. The key principles are based on coercion-free and informed choice; neutral, understandable and evidence-based information; collaborative and confidential decision-making process; ensuring respectful care, dignity and choice*. The definition took into consideration the core dimensions articulated in the literature and mirrors the principles that were deliberated by the think tank: a two-way discussion and decision-making process between the client and provider, sharing objective and user-friendly information, and fundamentally grounded in the rights to autonomy, dignity, privacy, respect and participation, among others. In addition, person-centeredness is a critical component of quality in family planning.^5^ The four-item person-centred contraceptive counselling scale (PCCC) is a valid and reliable measure of person-centred contraceptive counselling that reflects patients’ perspectives on contraceptive counselling.^34^ For example, integrating Dehlendorf’s four-item validated tool: PCCC: person-centred contraceptive counselling scale: Think about your visit. How do you think the member of the healthcare team did? Please rate them on each of the following by circling a number (the scale will use—Poor, Fair, Good, Very good and Excellent). Hence, to measure decision-making autonomy, the following considerations need to factor:

Respecting me as a person.Letting me say what mattered to me about my birth control method.Taking my preferences about birth control seriously.Giving me enough information to make the best decision about my birth control method.

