#### Eligibility criteria for clusters (health centers) and participants

The trial will take place in specific primary health centres that meet the eligibility criteria outlined in the pre-formative phase objectives. A woman can participate in the study if

She comes to the family planning clinic with the intention to (a) use contraception for the first time in her life (new user) or (b) switch from a contraceptive method to another one (switching user) or (c) resume a method after not using any in the prior 3 months (lapse user), or (d) discontinue a modern method (discontinuing user).She is not coming for the resupply of a currently used method, such as pills or injectables.She has the intention to continue her follow-up at the health centre during the 12-month study follow-up.She does not participate in another study.She provides informed consent.

Exclusion criteria: not willing to participate in the complete duration of the trial.

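### The autonomy rating taken straight after enrolment counselling plays no part in the stated arm comparison, which rests on 6- and 12-month ratings whose reference visit is not given

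*Protocol article*

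**What the plan says.** - **The tool.** The Background section of the protocol article gives the PCCC stem as "Think about your visit. How do you think the member of the healthcare team did", followed by four items on a five-category scale from poor to excellent.
- **Its role.** Under Outcome measures, autonomy is measured first by domain questions: "clients will be asked to answer questions about the different domains contained in the counselling definition". The PCCC comes in addition: "The PCCC, developed and tested in publicly funded clinics in California, will also be used". On its timing, the text says only that "it will be assessed during the intervention phase as per described by UNFPA to measure decision-making autonomy SDG 5.6.1".
- **The schedule.** For autonomy and demand satisfied: "The proposed outcomes to be assessed after each visit, at mid-point (6 months after enrollment) and at the study end (12 months after enrollment". The same section times modern contraceptive prevalence differently: after the first visit, then at 6 and 12 months.
- **The comparison.** The Statistical analysis section takes, within each arm, the difference between the 12-month and 6-month measurements and compares these changes between control and each experimental arm. It describes no other between-arm comparison. Participants are the unit of analysis.
- **Follow-up.** Eligibility requires that "She has the intention to continue her follow-up at the health centre during the 12-month study follow-up". It also requires that "She is not coming for the resupply of a currently used method".
- **The arms.** Arm 2 offers up to four methods and arm 3 more than four. Eligible centres provide both short- and long-term methods.

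**The concern.** The trial asks whether a counselling package raises decision-making autonomy. A tool that rates one encounter answers this best when it is put straight after the counselling, about the same encounter in every arm. The schedule provides for that rating, because the enrolment visit falls under each visit. The stated comparison then leaves it out and uses two later time points instead.

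At those later points the article does not say what a woman is rating. It could be the enrolment visit, her latest attendance or the study contact itself. If the contacts include no counselling, women who came back recently and women who never came back answer the same question about encounters of very different age. Method choice drives return frequency, and arm 3 widens the choice of methods by design, so the imbalance could differ by arm. A null result on the 12-minus-6-month change could then reflect the timing of the rating and not the package. An effect already present at 6 months and held to 12 months would also cancel out of the change.

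**Working it through.** The plan gives no figure on this point, so there is none to reproduce. The check has two parts.

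**1. What the stated comparison uses**

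| Autonomy rating | Scheduled? | Reference visit clear? | Used in the 12-minus-6-month change? |
|---|---|---|---|
| On leaving enrolment counselling | Yes (after each visit) | Yes | No |
| After later visits | Yes (after each visit) | Yes, but type of visit not defined | No stated role |
| Month 6 | Yes | Not stated | Yes |
| Month 12 | Yes | Not stated | Yes |

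The article times contraceptive prevalence after the first visit but autonomy after each visit. The two phrases are kept apart, so the autonomy schedule cannot be read as meaning the enrolment visit alone. The month-6 and month-12 ratings are also listed separately from the after-visit ratings. The only row with both a clear referent and a direct link to the enrolment counselling is one that the comparison does not use.

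**2. How far recall could vary if the fixed contacts include no counselling**

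Return intervals are assumed; the article gives none. Visits fall at month 0 and every k months up to month 12. Recall at month T is T minus the month of the last visit. The lower end assumes a visit on the day and the upper end a rating just before the next visit.

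| Assumed return interval | After-visit ratings in 12 months | Recall at month 6 | Recall at month 12 |
|---|---|---|---|
| 1 month | 13 | 0–1 month | 0–1 month |
| 3 months | 5 | 0–3 months | 0–3 months |
| 6 months | 3 | 0–6 months | 0–6 months |
| No return | 1 | 6 months | 12 months |

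Recall therefore spans 0 to 12 months. For these intervals, its range is the same at both points for women who return, and it lengthens by 12 − 6 = 6 months only for women who do not. The false between-arm difference in the 12-minus-6-month change is then:

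difference in share of non-returners × drift per month of recall × 6

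Both inputs are assumed. The share differs by 5 to 20 percentage points, and drift is 0.01 to 0.05 points per month on an item scored 1 to 5:

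- low: 0.05 × 0.01 × 6 = 0.003 points
- middle: 0.10 × 0.02 × 6 = 0.012 points
- high: 0.20 × 0.05 × 6 = 0.06 points

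If the 6- and 12-month contacts do include counselling, recall is about 0 for every woman at those points and this term disappears. Part 1 is unaffected.

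**The case against.** Several stronger readings are tempting, and the article does not support them.

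- **That there is no counselling visit to rate at 6 and 12 months.** Nothing in the text says so. Women are expected to be followed at the health centre and each centre has a research assistant, which is compatible with clinic contacts that include counselling. The caption of Figure 3 reads "Schedule of enrolment, interventions and assessments for the cluster randomised controlled trial phase in each study country (SPIRIT template", but the figure itself is not visible here, and that is not a fault of the plan. The recall problem is therefore conditional.
- **That frequent returners dominate a pooled score, so method mix alone separates the arms.** This would need ratings to be the unit of analysis. The plan makes participants the unit and gives after-visit ratings no role in the comparison. Nor does it say that a later resupply attendance counts as a visit for this purpose; the resupply criterion governs entry only.
- **That the whole autonomy measure refers to a visit.** The PCCC is only part of it. The domain questions are given no stem, and the PCCC is not expressly scheduled at 6 and 12 months. This does not rescue the comparison. If the PCCC is asked only after visits, the 12-minus-6-month change does not use it at all.

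The strongest general objection is that reference visits, visit windows and scoring belong in the case-report forms, the study manual and the announced analysis plan. For wording and scoring details that is fair, and their absence here is no fault. But the article itself states both the assessment times and the comparison, and that comparison omits the enrolment rating. Which encounter a woman is asked about is also fixed when the question is put, and analysis cannot recover it afterwards.

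**Conclusion.** The point holds in a limited form. As stated, the arm comparison for autonomy does not use the rating tied most closely to the intervention, and it relies on two time points for which the visible text names no reference visit. That follows from the article's own sections without assumptions.

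The recall effect rests on three: that the visit-referenced items are asked at 6 and 12 months, that no counselling takes place then, and that return patterns differ between arms. Recall could then range from 0 to 12 months, but the illustrated false difference in change is at most 0.06 points on an item scored 1 to 5. The main cost is thus a poorly chosen comparison for the objective, with recall bias a smaller and conditional addition. The change is cheap and worth making.

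**What to change.** - Define the autonomy outcome as one score per woman, from the domain questions and the PCCC, taken on leaving the enrolment counselling visit. Compare that level between control and each experimental arm, allowing for clustering.
- Keep the 6- and 12-month autonomy assessments for all women as secondary outcomes, and name in the question the visit being rated. Do not limit them to women who had a further counselling visit. That would select on an event after randomisation which arm 3 may itself affect.
- Keep demand satisfied and modern contraceptive use as 6- and 12-month outcomes.

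**Cost.** The rating is already scheduled, so no interview is added. The case-report forms and outcome definition need new wording, and the 12-minus-6-month comparison must be rewritten for this outcome. The repeat autonomy ratings become secondary, so whether autonomy lasts is no longer the main question. If the sample size was worked out for a change, it should be rechecked for a level; the article shows no derivation from which to do that.
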